**Secondary:**

- To compare the average amplitude of N80 and N150 in the groups (intervention and control), between before and after the intervention.
- To compare the average amplitude of N80 and N150 between the groups (intervention and control) before and after the intervention.
- To compare the average active motor threshold of the multifidus and transverse abdominis muscles in the groups (intervention and control), between before and after the intervention.
- To compare the average active motor threshold of the multifidus and transverse abdominis muscles between the groups (intervention and control) before and after the intervention.
- To compare the average amplitude of the motor-evoked potentials (MEPs) of the multifidus and transverse abdominis muscles in the groups (intervention and control), between before and after the intervention.
- To compare the average amplitude of the motor-evoked potentials (MEPs) of the multifidus and transverse abdominis muscles between the groups (intervention and control) before and after the intervention.
- To examine the correlation between clinical parameters and brain neurophysiological parameters.

**5. Research Questions and Hypotheses**

- Is there a difference in the average amplitude of N80 and N150 in the groups (intervention and control) between before and after the intervention?
- Is there a difference in the average amplitude of N80 and N150 between the groups (intervention and control) before and after the intervention?
- Is there a difference in the average active motor threshold of the multifidus and transverse abdominis muscles in the groups (intervention and control) between before and after the intervention?
- Is there a difference in the average active motor threshold of the multifidus and transverse abdominis muscles between the groups (intervention and control) before and after the intervention?
- Is there a difference in the average amplitude of the motor-evoked potentials (MEPs) of the multifidus and transverse abdominis muscles in the groups (intervention and control) between before and after the intervention?
- Is there a difference in the average amplitude of the motor-evoked potentials (MEPs) of the multifidus and transverse abdominis muscles between the groups (intervention and control) before and after the intervention?
- Is there a difference in the average level of lumbar movement control in the groups (intervention and control) between before and after the intervention?
- Is there a difference in the average level of lumbar movement control between the groups (intervention and control) before and after the intervention?
- Is there a difference in the average level of disability in the groups (intervention and control) between before and after the intervention?
- Is there a difference in the average level of disability between the groups (intervention and control) before and after the intervention?
- Is there a difference in the average level of pain in the groups (intervention and control) between before and after the intervention?
- Is there a difference in the average level of pain between the groups (intervention and control) before and after the intervention?
- Is there a significant correlation between clinical parameters and brain neurophysiological parameters?

**6. Practical Implications**

If combining exercises with tDCS yields better results, this method could be recommended for clinical use. If there is little difference between the treatment groups, it could be suggested that exercises alone are effective, thus avoiding additional costs, or seeking a new treatment method.

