**14. Inclusion Criteria**

- Age between 20 and 50 years
- Both male and female genders
- Chronic low back pain for more than 6 months, or 3 episodes of low back pain lasting more than one week in the past 12 months
- Unilateral radicular pain secondary to disc herniation at L4/L5 and L5/S1, confirmed by MRI
- Positive result in at least one of the tests: Slump test, Straight Leg Raise, or Lasegue’s sign
- Pain radiation from the anterior posterior calf to the area behind the leg associated with the L4/L5 dermatome to the posterior calf to the heel and outer part of the foot
- Average pain intensity must be 4 or more according to the Numerical Pain Scale
- Average disability score based on the Oswestry Disability Index must be 4 or more
- No spinal tumors
- No cognitive disorders according to Mini Mental Status Examination score ≥ 24
- No spondylolisthesis or spondylolysis
- No structural disorders or spinal deformities such as scoliosis, kyphosis, or severe lordosis
- No spinal fractures
- No brain injuries, including concussions or strokes
- No neurological diseases such as Parkinson’s disease, Alzheimer’s disease, or cerebellar disorders
- No scalp skin lesions or cuts
- No sensory disturbances or loss
- No history of epilepsy
- Not pregnant
- No metallic implants in the brain
- No skin infections
- No pacemakers or other implanted devices
- No visual disturbances
- No depression requiring medication
- No previous spinal surgeries

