**16. Data Collection Tools**

- Recording sensory evoked potentials with the EMG/NCV/EP5000 Q device
- Recording motor evoked potentials with the TMS MagPro X100 device
- Assessment of low back motor control using Luomajoki clinical tests
- Measurement of disability using the Persian version of the Oswestry Disability Index questionnaire
- Measurement of pain with the Visual Analog Scale (VAS)
- Cognitive assessment using the Mini Mental Status Exam (MMSE)
- Recording demographic and clinical characteristics with a designed questionnaire
- Consent form

**17. Procedure**Initially, the study will receive an ethics code and will be registered in the IRCT system to obtain a clinical trial code. Participants who meet the study criteria will be given detailed explanations about the research procedures so they have a full understanding of how the study will be conducted. Each participant will provide informed consent by signing a written consent form approved by the Tehran University of Medical Sciences Ethics Committee. Assessments will be conducted first, followed by treatments in the control group (sensory-motor exercises combined with sham transcranial electrical stimulation) and the intervention group (sensory-motor exercises combined with real transcranial electrical stimulation) for 4 weeks. Reassessment will occur 24 to 48 hours after the last treatment session.

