**17-2. Treatments**

After the initial assessment, individuals will be randomly assigned to one of two groups. The sequence will be generated using the website randomization.com with a balanced block randomization method. The block size will be 4. To ensure allocation concealment, sealed and numbered envelopes will be used, which will be provided to participants by the secretary. The treatment period for both groups will be 12 sessions, three times a week. After the treatment period, evaluations will be conducted again.

Due to the inclusion of a sham treatment, participants will be blinded, but blinding of the therapist or evaluator will not be possible.

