**17-2-1. Control Group**

In this group, participants will receive sensory-motor exercises combined with sham transcranial electrical stimulation for 4 weeks, three times a week (12 sessions). Participants will first receive the sham stimulation and then perform the exercises.

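### Section 6 suggests that little difference between the arms could mean exercises alone are effective; with exercise in both arms and 15 to 17 patients per arm, the design does not support that reading

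*Protocol*

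**What the plan says.** Section 6 (Practical Implications) covers two outcomes. If the combination does better, it could be recommended for clinical use. Otherwise: "If there is little difference between the treatment groups, it could be suggested that exercises alone are effective, thus avoiding additional costs". The sentence then offers a second reading, "or seeking a new treatment method". It does not define a little difference, and it gives no rule for choosing between the two readings.

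Section 17-2 states that "individuals will be randomly assigned to one of two groups". In the control arm, "participants will receive sensory-motor exercises combined with sham transcranial electrical stimulation for 4 weeks" (section 17-2-1). The intervention arm has the same exercise schedule with real stimulation (section 17-2-2). No arm goes without exercise, and no arm has exercise without a sham.

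Section 13 sizes the trial on pain with a between-group Cohen's f of 0.473, power 0.8 and α 0.05, giving 30 needed and 34 recruited. Section 18 plans a two-way mixed ANOVA and labels η² as small, medium or large. No equivalence or non-inferiority margin appears. Sections 4 and 5 also list before-after comparisons within each group.

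**The concern.** The suggested reading contains two inferences, and the design supports neither.

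- **Exercise is effective.** Exercise is common to both arms and cancels out of the randomised contrast. Similar results are expected if exercise works in both arms, and equally if it works in neither.
- **The cost of tDCS can be saved.** This needs evidence that any tDCS benefit is too small to matter. A small observed difference in a small trial is not such evidence unless the confidence interval is narrow against a stated margin.

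A null or near-null result could therefore be turned into a favourable statement about exercise and an economic argument against tDCS, neither resting on the randomised data.

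**Working it through.** **Inputs from the protocol.** f = 0.473, power 0.8, α 0.05, 30 needed and 34 recruited (section 13); two arms in "balanced block randomization method. The block size will be 4" (section 17-2), taken as 1:1, so 15 to 17 per arm; mixed ANOVA with two time points (section 18); at entry, "Average pain intensity must be 4 or more according to the Numerical Pain Scale" (section 14).

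**Assumed, because the protocol gives no figure.** Pre-post correlation ρ of 0.5, with a range of 0.3 to 0.7; equal SD in both arms and at both times.

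**1. The plan's own figure.** For the between-group factor of a repeated-measures ANOVA with m = 2 measurements, the noncentrality is λ = f²·N·m / (1 + (m−1)ρ). At ρ = 0.5 and N = 30, λ = 0.2237 × 30 × 2 / 1.5 = 8.95, and power is 0.823. N = 28 gives 0.794. The stated 30 is reproduced. For two groups d = 2f = 0.946, so the target is a large effect.

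**2. What an observed difference of zero would leave open.** 95% half-width in SD units:

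- change scores (the group-by-time test): t(0.975, 2n−2) × √(2/n) × √(2(1−ρ))
- ANCOVA, for comparison: t(0.975, 2n−3) × √(2/n) × √(1−ρ²)

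For change scores at n = 15 and ρ = 0.5: 2.048 × 0.3651 × 1 = 0.748.

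| Analysis | ρ | 15 per arm | 17 per arm |
|---|---|---|---|
| Change score | 0.3 | 0.885 | 0.827 |
| Change score | 0.5 | 0.748 | 0.699 |
| Change score | 0.7 | 0.579 | 0.541 |
| ANCOVA | 0.3 | 0.715 | 0.667 |
| ANCOVA | 0.5 | 0.649 | 0.606 |
| ANCOVA | 0.7 | 0.535 | 0.4996 |

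**3. Power against smaller effects.** For a two-sample comparison (noncentral t; the same as change scores at ρ = 0.5), power is 26% at 15 per arm and 29% at 17 for a true benefit of 0.5 SD, and 56% and 62% for 0.8 SD. The effect detectable with 80% power is 1.06 SD and 0.99 SD.

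**4. What showing no worthwhile effect would take.** With an illustrative margin of 0.5 SD, a true difference of zero, one-sided 0.025 and 80% power: n = 2 × ((1.960 + 0.842) / 0.5)² = 62.8, so 63 per arm.

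**5. Why within-arm change does not help.** Suppose pain in the source population is normal with mean 5 and SD 2, and entry requires 4 or more (all but the cut-off assumed). The cut-off lies 0.5 SD below the mean, and φ(0.5)/Φ(0.5) = 0.509. The entry mean is then 5 + 2 × 0.509 = 6.02. The expected fall with no treatment effect is (1−ρ) × 1.02, or about 0.5 points at ρ = 0.5 (0.7 at ρ = 0.3, 0.3 at ρ = 0.7). This treats the numerical scale used at entry and the VAS used as outcome as one measure. It is an illustration, and sham response and natural course come on top.

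**The case against.** The strongest reply is that this is one hedged sentence in a rationale section. It says only what could be suggested, it goes on to a second reading that does not assume exercise works, and no test or sample size depends on it. All of that is true. But a hedge does not make an inference valid, and the second reading shows the difficulty: the same result is allowed to point either way, with nothing to decide between them.

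A second reply is that section 8 summarises earlier studies of sensory-motor exercise, some with a control group. That background could support a view on exercise. It would be evidence from those studies, however, and section 6 ties the suggestion to this trial's between-group difference.

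A third is that the η² bands in section 18 define a small effect. They label a point estimate and do not say what the data exclude.

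A reader might also infer more than the text supports:

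- That the protocol treats a non-significant p-value as proof of no effect. Section 6 does not mention significance; its criterion is simply undefined.
- That this is the protocol's only statement on interpretation. Section 6 also covers a better result, and section 18 has the η² bands.
- That a 0.5 SD benefit could never be excluded. With 17 per arm, ANCOVA and ρ = 0.7 the half-width is 0.4996 SD, so it just is. That is an edge case, and ANCOVA is not the planned analysis.

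**Conclusion.** The point holds as a fault in a stated conclusion, not in the analysis or, on this issue, in the sample size. The failure to inform on exercise follows from the two-arm design alone and needs no assumption. The imprecision on tDCS rests on the assumed correlation and the choice of analysis: about 0.75 SD at 15 per arm and 0.70 SD at 17 for change scores at ρ = 0.5, and roughly 0.50 to 0.89 SD over all combinations shown. Throughout that range, a result with no observed difference remains compatible with a moderate tDCS benefit, and under most of the assumptions with one clearly above 0.5 SD. The documents do not show that the sponsor has committed to publishing a claim for exercise or a recommendation against tDCS. They show that the protocol offers this reading and that the trial could not back it.

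**What to change.** Replace the sentence in section 6 on little difference with:

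> If there is little difference between the groups, the trial will report that no added benefit of tDCS was demonstrated, with the 95% CI for the between-group difference in pain change. Absence of a worthwhile tDCS effect will be claimed only if that CI excludes a difference fixed before the outcome data are analysed. No conclusion on the effectiveness of exercise will be drawn from this trial, because both groups receive it.

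The margin is tied to the start of analysis, not to unblinding, because section 17-2 says the therapist and evaluator cannot be blinded. The interval for pain change matches the group-by-time comparison already planned, so no new model is needed. In sections 4 and 5, mark the within-group before-after comparisons as descriptive only, since they are the other route to the same inference.

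The cost is wording: no added patients, visits or data. The sponsor gives up a conclusion that the design does not support, and should expect that 15 to 17 per arm will seldom be enough to claim absence of a worthwhile effect.

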**7. Novelty of the Study**

Studies indicate that tDCS and sensory-motor exercises may positively affect pain reduction in patients with chronic low back pain. However, as noted, sensory and motor processing in the brain is disrupted in these patients. This aligns with other behavioral evidence indicating issues in sensory-motor control of the back in these individuals, which can ultimately lead to disability. Sensory-motor control is considered a key factor in the progression and recurrence of low back pain. Despite the significance of brain changes in sensory and motor areas and disruptions in sensory-motor control, no study has yet examined the effects of anodal tDCS on sensory and motor areas combined with sensory-motor exercises on brain processing and improvement in sensory-motor control in these patients. This study aims to assess for the first time the impact of anodal tDCS on the M1 and S1 regions, combined with exercises, on improving the mentioned parameters. The goal is to determine whether stimulating these regions with anodal tDCS, combined with exercises, can be a more effective treatment for individuals with chronic low back pain, considering the decreased excitability of the M1 and S1 areas in these individuals. The study will also focus on neurophysiological parameters in addition to clinical parameters, seeking to uncover potential mechanisms and understand the relationship between improvements in clinical parameters and changes in neurophysiological parameters, which has not been addressed before.

**8. Review of Previous Studies**

This section reviews previous articles in several subcategories:

- Effect of Combining Transcranial Electrical Stimulation (tDCS) with Sensory-Motor Exercises
- Effect of Combining tDCS with Other Exercises
- Effect of tDCS on Pain
- Effect of Sensory-Motor Exercises on Brain Reorganization
- Effect of Sensory-Motor Exercises on Pain and Muscular Function

**Effect of Combining tDCS with Sensory-Motor Exercises:**

- Adam Louis Ouellette and colleagues published a protocol in 2017 for a double-blind clinical trial. In this study, 80 patients with chronic low back pain were randomly assigned to two groups: real tDCS + sensory-motor exercises and sham tDCS + sensory-motor exercises. tDCS was applied for 20 minutes to the primary motor cortex along with 60 minutes of sensory-motor exercises twice a week for a total of 10 weeks. Feasibility (including the number of treatment sessions per patient, dropout rates, participant interest in continuing treatment, and completion of home exercise sessions), safety, pain, disability, and individual performance before and after the 10-week treatment were evaluated. The goal was to assess the efficacy of this treatment protocol (31).

**Effect of combining tDCS with Other Exercises:**

- Jafarzadeh and colleagues in 2019 studied the short-term and long-term effects of combining anodic tDCS and postural exercises in patients with low back pain and postural disorders. 38 individuals were divided into three groups: real anodic tDCS with exercises, sham anodic tDCS with exercises, and exercises alone. All participants received postural exercises three times a week for 20 minutes over two weeks. Anodal current was applied with 2 milliamperes for 20 minutes to the M1 area. Postural stability, balance, and pain were measured before, immediately after, and one month after the intervention. Significant improvements in balance, stability, and pain were observed in the group receiving real anodic tDCS with postural exercises, with no differences in other groups. The results indicate that anodic tDCS combined with postural exercise is effective in improving balance, stability, and pain in patients with low back pain and postural disorders, whereas postural exercises alone are insufficient to improve postural disorders (38).
- A double-blind pilot clinical trial by Sofia Straudi and colleagues in 2018 involved 35 patients with non-specific chronic low back pain receiving either five sessions of real or sham brain stimulation combined with ten sessions of group exercise. VAS, Rolland Morris questionnaire, EuroQuol-5, and patient health questionnaires were assessed. A significant difference in pain intensity and patient health questionnaires was found one month after combined treatment (39).
- A protocol study by Cavalcante and colleagues in 2020 examined the combination of tDCS with exercise therapy. They predicted that 60 patients with chronic low back pain would receive combined treatment (1-real tDCS + exercises or 2-sham tDCS + exercises) over 12 sessions across 4 weeks. Pain intensity, emotional and sensory aspects of pain, physical function, and fear of movement were assessed before, after, 3 months, and 6 months post-treatment. The exercises included stretching, strengthening, and motor control (40).
- A pilot double-blind study by Yuanbo Ma and colleagues in 2020 investigated the effect of high-definition tDCS and strengthening exercises for the plantar sensation and dynamic balance in individuals with chronic ankle instability. 30 adults were treated for four weeks with tDCS applied to facilitate excitability in the M1 and S1 areas. The combination of treatments improved dynamic balance and proprioception (41).
- A double-blind study by Mendonca and colleagues in 2016 aimed at modulating the motor system in fibromyalgia patients combined tDCS on M1 with aerobic exercises. 45 patients were divided into three groups (1-exercise + tDCS, 2-exercise only, 3-tDCS only). Dependent variables included pain intensity, anger, quality of life, mood, pressure pain threshold, and cortical plasticity. No significant differences in cortical plasticity were found among the groups, but the combination of tDCS and exercise had significant effects on pain, anger, and mood (42).

**Effect of tDCS on Pain:**

- In a double-blind study by Fuad Ahmad Hazime and colleagues in 2017, 92 patients with non-specific chronic low back pain were divided into four groups: (1-real tDCS + real peripheral stimulation; 2-real tDCS + sham peripheral stimulation; 3-sham tDCS + real peripheral stimulation; 4-sham tDCS + sham peripheral stimulation). Treatments were administered over 4 weeks with three sessions per week (total 12 sessions). Pain was assessed before, during, and after sessions. Real tDCS was applied at 2 milliamperes for 20 minutes, with active electrodes on C3 and C4, and sham electrodes on the supraorbital area. Peripheral stimulation was applied as a non-symmetric, rectangular biphasic current with 100 Hz frequency and 200 microseconds pulse duration for 40 minutes on the most painful part of the back. The study concluded that combining tDCS with peripheral stimulation could be effective in reducing low back pain in the long term, whereas tDCS alone did not significantly reduce pain (20).
- Timothy Y. Mariano and colleagues in 2018 conducted a double-blind study involving 30 patients with chronic low back pain divided into placebo and control groups. During ten treatment sessions, cathodal tDCS at 2 milliamperes for 20 minutes was applied to the FC1 area. Improvements in pain and depression were observed after treatment (43).

**Effect of Sensory-Motor Exercises on Brain Reorganization:**

- Bae and colleagues in 2014 studied 14 individuals (7 healthy and 7 with chronic low back pain). The study aimed to examine the effect of sensory-motor exercises on anticipatory postural control settings, brain changes in motor cortex areas using EEG, and the onset of contraction in the transverse abdominal and external oblique muscles using EMG, as well as pain. Patients with chronic low back pain were in the experimental group and performed exercises for 4 weeks, 4 sessions per week. Significant changes were observed in EEG parameters including readiness potential, motor potential, and movement monitoring potential. Reductions in readiness and motor potentials were noted in the relevant motor cortex areas, and significant differences in the onset of contraction in both muscles were found. Pain levels also decreased significantly (33).
- Rocco Cavaleri and colleagues in 2020 randomly divided 30 healthy individuals into two groups. Participants attended a single visuomotor exercise session divided into three phases (baseline, test, and recovery). Corticomotor responses were assessed twice in the baseline phase. In the test phase, one of two exercises (lumbo-pelvic tilt for the test group or repeated finger abduction for the control group) was performed for 15 minutes. Corticomotor responses were evaluated using TMS. In the recovery phase, the persistence of any corticomotor adaptation was assessed at 15 and 30 minutes post-exercise. The study found no significant correlation between corticomotor organization and performance improvements, suggesting that changes were more related to subcortical or spinal networks rather than corticomotor pathways. The researchers recommended further studies with varying complexities and durations (44).

